#### Control group (pomanipulative therapy group)

Pseudomanipulative therapy involves light touching on the patient’s neck muscles, starting with kneading to relax the muscles, moving the hand every 5 s to prevent the patient’s body from reacting mechanically to prolonged force or touch, and relaxing the hand during treatment to reduce the concentration of stress without pressing too much on pressure points or muscle striae nodules. During the manipulation process, the pressure applied should not be too heavy; gentle pressure should be used, with each muscle being pressed for no more than 5 s. When performing cervical fixed-point rotation manipulation, it is not necessary to locate the affected cervical spine segment. Under the premise of ensuring safety, there is no requirement for the angle, force, or accuracy of the maneuver, and the joint popping sound produced by the trigger is not pursued. To ensure the implementation of the patient’s blind method, the two treatment implementers will be required to maintain a similar maneuver to ensure the same contact time. It is guaranteed that the subjects will not contact with the manipulation operator outside of the treatment session. The course of treatment will be as follows: once every other day, three times a week, four consecutive weeks of treatment, for a total of 12 times. Follow-ups will be conducted 1 month and 6 months after the end of treatment.

#### Western medicine group

Mecobalamin (Eisai China Pharmaceutical Co., Ltd., 500 μg/tablet) 500 μg/dose, 3 times a day, supplemented with celecoxib capsules (Pfizer Pharmaceutical Co. Ltd., 0.2 g/capsule) 0.2 g/d, 1 time/d, for pain relief in those with obvious pain, for a duration of 4 weeks. Follow-ups will be conducted one month and six months after the end of treatment.

### Outcome measures

#### Primary outcome

HRV-Related Parameters: This study will utilise a 24-h ambulatory electrocardiograph to measure three distinct groups of HRV parameters, both prior to and following treatment. The primary parameters will be evaluated encompassed the standard deviation of the mean of the R-R intervals per 5-min segment (SDANN), the standard deviation of the R-R intervals (SDNN), the proportion of neighboring R-R interval differences greater than 50 milliseconds as a percentage of the total number of heartbeats (PNN50), and the root mean square of the neighboring R-R interval differences (rMMSD).

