**Methods/design:**

In this study, 90 participants will be randomly assigned at a 1:1:1 ratio into a test group (cervical fixed-point rotational manipulation manipulation group), a control group (sham manipulation group), or a Western medicine control group, with 30 participants in each group. All participants will be treated for a period of 4 weeks. The primary outcome indicators assessed is the HRV-related parameters, and the secondary outcome indicators are the NDI scale, NPQ scale, and HAMA scale. The assessment time points will be before and after treatment. The follow-up visits will be the first and sixth months after the end of treatment.

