### Trial design

The main objective of this study is to observe the effect of cervical localized rotation manipulations on heart rate variability in patients with SCS. Through 24-h ambulatory electrocardiogram, changes in HRV during the treatment of sympathetic cervical spondylopathy can be observed more intuitively and objectively. To evaluate the efficacy of cervical fixed-point rotation manipulations more objectively, a pseudomanipulative therapy group will be added to the test group for the control group, and it will be observed whether there is a difference in efficacy between cervical fixed-point rotation manipulations and pseudomanipulative therapy to further clarify the efficacy of cervical fixed-point rotation manipulations.

This study is a randomized controlled trial conducted at Zhejiang Hospital to assess the effect of cervical fixed-point rotation manipulations on heart rate variability in patients with SCS. A total of 90 participants with SCS who meet the criteria will be randomly assigned to the test group (cervical fixed-point rotation manipulation group), control group (pseudomanipulative therapy group), or Western medicine group. The study has been registered on the International Traditional Medicine Clinical Trial Registry, which is accredited by the World Health Organization as a Level 1 registry, at the following URL: http://itmctr.ccebtcm.org.cn/ (the Clinical trail number: NO. ITMCTR2025000569). The protocol reporting will adhere rigorously to the SPIRIT guidelines (33). The process of the study is illustrated in Figure 1, which presents a flowchart. Furthermore, the schedule for the enrollment, treatment and assessment of the trial is show in Figure 2.

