#### Statistical analysis

The data obtained in this study will be entered into the Excel database by two independent persons, and the data will be analyzed by statisticians through SPSS (Statistical Product and Service Solutions) 20.0 statistical analysis software. Count data will be analyzed via the X2 test and the rank sum test for rank data. Measurements will be first tested for normality via the Shapiro–Wilk test, and measurements that conformed to a normal distribution were described via the mean plus minus standard deviation (X ± S). Comparisons between pre- and posttreatment values within groups will be made via the paired-samples t test, and comparisons before and after treatment between groups will be made using the performed via one-way analysis of variance (ANOVA). The results will be analyzed, with *p* < 0.05 as the judgment criterion for significant differences. The rank sum test will be used for nonconformity to a normal distribution.

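### Four co-equal primary HRV parameters with no success rule, one unadjusted 0.05 criterion, and an omnibus ANOVA that does not by itself answer test versus sham

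*Protocol article*

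**What the plan says.** The Abstract treats the primary outcome as a set: "The primary outcome indicators assessed is the HRV-related parameters". Primary outcome lists its members: "The primary parameters will be evaluated encompassed the standard deviation of the mean of the R-R intervals per 5-min segment (SDANN"), then SDNN, pNN50 and rMSSD, measured by 24-hour ambulatory ECG before and after treatment. None is placed first, and nothing says whether one, some or all must show an effect.

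Statistical analysis sets a single criterion for all results, "with *p* < 0.05 as the judgment criterion for significant differences", and mentions no adjustment. It names three procedures for measurements:

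- Within arms: "Comparisons between pre- and posttreatment values within groups will be made via the paired-samples t test".
- Between arms, for normal data: "comparisons before and after treatment between groups will be made using the performed via one-way analysis of variance (ANOVA").
- Otherwise: "The rank sum test will be used for nonconformity to a normal distribution". It does not say whether this is a two-group or a three-group test.

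Trial design gives the reason for the sham arm: "it will be observed whether there is a difference in efficacy between cervical fixed-point rotation manipulations and pseudomanipulative therapy".

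**The concern.** Two gaps meet in the primary analysis.

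1. **Four primaries and no success rule.** The four parameters carry equal rank and each is tested at 0.05. The choice of which result counts as the trial's answer is left open until the data are in. If one out of four is then accepted, the error rate is above 5%.
2. **The named test and the stated question differ.** A three-arm F test asks whether any of the three means differ. The stated question is whether manipulation differs from sham. The paired t tests do not compare arms at all.

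The Conclusion says the results will be used to determine efficacy and may change conservative treatment. As the text stands, a report could rest that claim on one parameter of four, or on an F test driven by the drug arm.

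**Working it through.** **Plan's own figure.** Statistical methods sizes the trial with λ = 12.65 (2 degrees of freedom, α = 0.05, β = 0.10), Pmax = 0.85 and Pmin = 0.40.

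- 2·asin√0.85 − 2·asin√0.40 = 0.9768.
- n = 2 × 12.65 / 0.9768² = 26.5 (printed 26.6), taken as 27.
- 27 / 0.9 = 30 per arm, 90 in all.

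This reproduces. It rests on a three-group comparison of effective rates, so it supplies neither a lead HRV parameter nor a test-versus-sham contrast. It is used below only for the arm size.

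**Inputs.** From the article: four primary parameters, three arms, 27 evaluable (30 randomised) per arm, 0.05 per test. Assumed, because the article does not give it: the correlation among the four parameters.

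**Step 1. At least one of four F tests significant when nothing works.**

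For independent parameters: 1 − 0.95⁴ = 1 − 0.8145 = 18.5%.

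For correlated parameters, four jointly normal outcomes were simulated in three arms with no effect:

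| Assumed common correlation | 0 | 0.5 | 0.7 | 0.9 |
|---|---|---|---|---|
| At least one significant F, 27 per arm | 19% | 16% | 13–14% | 9–10% |
| At least one significant F, 30 per arm | 18.2% | 15.9% | 13.4% | 9.6% |
| At least one contrast of test with either control, read only after its own F is significant, 27 per arm | 16% | 13% | 11% | 8% |

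At correlation 0.95 the F-test figure is 8.0% (30 per arm). With two tightly correlated pairs (0.85–0.95 within pairs, 0.4–0.7 between) it is 10.6–13.7%. These counts leave out the 4 × 3 = 12 within-arm paired t tests.

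**Step 2. The opposite success rule.** If all four had to be significant, the error could not exceed that of any single test, so it stays at or below 5%. In simulation it was 0–2%.

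**Step 3. What a significant F shows.** Let manipulation equal sham exactly, and let only Western medicine differ by d standard deviations (d is assumed).

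- Means (0, 0, d): the sum of squared deviations is 2d²/3, so the noncentrality is n × 2d²/3.
- n = 30: 20d² = 5, 12.8 and 20 for d = 0.5, 0.8 and 1.0. The F test is significant in 49, 89 and 98% of trials.
- n = 27: 18d² = 4.5, 11.5 and 18. It is significant in 45, 86 and 97%.

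So a significant F is quite compatible with manipulation doing nothing beyond sham.

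**Step 4. Error after correction.** Testing each of four parameters at 0.05/4 = 0.0125 gives 1 − 0.9875⁴ = 4.9% under independence, and at most 4 × 0.0125 = 5% under any correlation.

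**The case against.** **No at-least-one rule is written down.** A reader might infer that the trial's false-positive risk is 9–19%. The article does not support that, because it gives no success rule at all. The range is conditional on accepting any one parameter. Its top end also needs independent parameters, which is implausible: pNN50 and rMSSD are both built from neighbouring R-R differences. This objection stands, and the figures are stated conditionally for that reason.

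**A larger figure is tempting.** If test versus sham and test versus Western medicine were read at 5% on all four parameters regardless of the F tests, the error would be about 32, 26–27, 23 and 17% at correlations 0, 0.5, 0.7 and 0.9. The article describes no such procedure. A contrast read only after a significant F cannot have a higher error than the F test itself. The figures that apply to that reading are the 16/13/11/8% in the table.

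**ANOVA is not the only between-group route.** Non-normal data go to a rank sum test. That is correct, but its form is not stated, so it does not clearly supply the test-versus-sham comparison.

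**Pairwise tests may be in the analysis plan.** This is a condensed article, and follow-up tests after an ANOVA are often left to the fuller document. One cannot conclude that the trial has no planned test of manipulation against sham, only that this document names none. A three-arm F test is also a legitimate first step: with three groups, pairwise tests made only after a significant F control the error within one parameter. They do nothing about the spread over four parameters.

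**SDNN might look like the natural lead.** The Background does not single it out. The same paragraph also names HF, RMSSD and pNN50, and describes SDANN as sensitive to sympathetic function, though with vagal influence.

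**Conclusion.** The point holds in limited form. The article itself fixes four equal primaries, gives no success rule, applies one unadjusted 0.05, and names for normal data an omnibus test that does not by itself answer the question in Trial design.

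If any one significant parameter counts as success, the chance of at least one false-positive F test runs from about 19% (independent) to 9–10% (correlation 0.9). With contrasts of test against each control read only after a significant F, it runs from about 16% to 8%. Both ranges assume normal outcomes and a correlation that the article does not give. Requiring all four would not inflate the error.

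The part about the four primaries is firm, because the number and rank of primary endpoints belong in the protocol. The part about the contrast is weaker: it is true of this document and might be settled in a plan not shown.

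**What to change.** Before unblinding, amend Primary outcome and Statistical analysis:

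1. Name one primary HRV parameter at end of treatment. Which one is the sponsor's choice. The other three become secondary.
2. Name one primary contrast, test versus sham, at two-sided 5%, and say which two-group form of the rank sum test replaces it if the data are not normal.
3. Test manipulation against Western medicine on the same parameter only if the first contrast succeeds. This fixed order needs no further adjustment.
4. If all four parameters must stay primary, apply Holm across the four test-versus-sham contrasts: smallest p-value against 0.0125, then 0.0167, 0.025 and 0.05, stopping at the first failure.

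The cost is wording only, with no extra data collection. The price is that three parameters lose primary status or, under Holm, that some power is lost.

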#### Secondary outcome

Cervical Dysfunction Index (NDI) and Neck Pain Questionnaire (NPQ): participants will be assessed for cervical spine function and pain via a questionnaire. The NDI is a significant instrument for the evaluation of cervical spine function. The NDI is categorized into four levels: 0–20% for mild dysfunction, 21–40% for moderate dysfunction, 41–60% for severe dysfunction, 61–80% for very severe dysfunction, and 90–100% for complete dysfunction. The NPQ Neck Pain Scale, on the other hand, uses a 9-point scale ranging from 0 to 100, with higher scores denoting more severe neck pain and conditions. An elevated score on the scale is therefore indicative of a more severe condition.Hamilton anxiety scale (HAMA): a questionnaire will be used to rate the patients’ anxiety symptoms. A total of 14 areas of questions are included to classify the anxiety factors into two categories: somatic and psychogenic. The main items are seven to thirteen for somatic anxiety and one to six and fourteen for psychogenic anxiety. All items of the HAMA are rated on a 5-point scale from 0–4, with the criteria for each level being (0) asymptomatic, (1) mild, (2) moderate, (3) severe, and (4) extremely severe, with a total of fourteen items to record a total score, with higher scores representing a more anxious state.

#### Follow-up observation

Patients will be monitored posttreatment, with follow-up assessments conducted at one month and six months. These assessments will be conducted either in person at the hospital or via telephone, and home visits will be arranged as necessary. The primary method of data collection involve the administration of questionnaires. For those demonstrating substantial improvement in panic and palpitations and significant changes in heart rate variability, an ambulatory electrocardiogram will be conducted at the time of follow-up to assess the long-term effects of manipulative therapy.

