#### Statistical methods

According to the prestudy observations, the best effective rate of the test group was 85%, the effective rate of the pseudomanipulative therapy control group was 40%, and the effective rate of the Western medicine group was 47%. The sample size estimation formula for the comparison of multiple sample rates was used to calculate P_max_ = 0.85, P_min_ = 0.40, *α* = 0.05, *β* = 0.10, and *ν* = 3–1 = 2, and the checking of the attached table yielded *λ* = 12.65. The number of sample cases was distributed between the groups according to a ratio of 1:1:1, and a unilateral test was used. *N* = 27 and considering a 10% shedding rate, 30 samples were needed in each group, for a total of 90 in the three groups.

$$n=\frac{2\lambda }{{\left(2\sin^{-1}\sqrt{P_{\max}}-2\sin^{-1}\sqrt{P_{\min}}\right)}^{2}}$$

$$=\frac{2\times 12.65}{{\left(\sin^{-1}\sqrt{0.85}-\sin^{-1}\sqrt{0.40}\right)}^{2}}$$

=26.6,take27

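### The 1- and 6-month ambulatory ECG is tied to having responded, so the follow-up HRV data cannot show a long-term effect of manipulation

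*Protocol article*

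**What the plan says.** The section Follow-up observation describes follow-up after treatment, "with follow-up assessments conducted at one month and six months", in person, by telephone or, where needed, at home. It adds: "The primary method of data collection involve the administration of questionnaires". The ambulatory ECG is then given to a subgroup: "For those demonstrating substantial improvement in panic and palpitations and significant changes in heart rate variability, an ambulatory electrocardiogram will be conducted", and this is done "at the time of follow-up to assess the long-term effects of manipulative therapy". The text shown gives no threshold for either condition and no direction for the HRV change. No other section shown provides a follow-up ECG for the remaining patients.

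HRV from the 24-hour ECG is the primary outcome. Under Primary outcome it is measured "both prior to and following treatment", with no condition on response. Statistical analysis plans paired tests within groups before and after treatment, and one-way ANOVA between groups. It does not mention the follow-up recordings separately.

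**The concern.** Whether a patient has the long-term HRV recording depends on two things observed after randomisation: symptom improvement, and change in HRV itself. This has two consequences.

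- **Within a group.** Patients chosen because HRV rose a lot from baseline to end of treatment will, on average, have had a baseline that was low by chance. Set against that baseline, their later values look like a kept benefit even if nothing worked.
- **Between groups.** The protocol expects response to differ by arm. The recorded patients would then be differently selected in each arm, and a contrast among them is no longer a comparison of randomised groups.

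At stake is any statement that the effect of manipulation on HRV lasts to 1 or 6 months. The gap arises at data collection, so no later analysis plan can fill it.

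**Working it through.** **The plan's own figures.** The documents give no number for the follow-up ECG subset, so there is none to reproduce. The related figures are the planning rates (85% test, 40% sham, 47% Western medicine) and the sample size under Statistical methods. The first line of the sample-size formula gives 2 × 12.65 / (2·asin√0.85 − 2·asin√0.40)² = 25.3 / 0.977² = 26.5, so 27 per arm (the article prints 26.6), and 27 / 0.9 = 30. The sample size holds and does not depend on the follow-up ECG.

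**Assumptions.** The documents give no HRV standard deviation, no correlation between recordings and no selection threshold. What follows is illustrative. It takes normal data and selection on a rise in HRV.

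**1. No treatment effect: apparent retained gain.** Let Y1, Y2 and Y3 be the baseline, end-of-treatment and follow-up values, each with SD 1 and a common correlation r.
- The SD of the change Y2 − Y1 is √(2(1 − r)).
- The slope of (Y3 − Y1) on (Y2 − Y1) is (1 − r) / (2(1 − r)) = 0.5.
- The mean change in the half with the largest rise is 0.798 × √(2(1 − r)). The mean gain at follow-up is half of that.

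| r | Mean change at end of treatment, selected half | Apparent retained gain at follow-up |
|---|---|---|
| 0.5 | 0.80 SD | 0.40 SD |
| 0.6 | 0.71 SD | 0.36 SD |
| 0.8 | 0.50 SD | 0.25 SD |

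The true gain is zero in every row.

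**2. A test-arm effect that has fully vanished by follow-up.** Take a true effect of 0.8 SD at end of treatment in the test arm and none in the sham arm, with selection if the change exceeds 0.5 SD. At follow-up the true gain is zero in both arms. The selected mean gain is 0.5 × √(2(1 − r)) × φ(a) / (1 − Φ(a)), where a = (0.5 − true effect) / √(2(1 − r)).
- r = 0.6, test: a = −0.335, so 0.5 × 0.894 × 0.597 = 0.27 SD.
- r = 0.6, sham: a = 0.559, so 0.5 × 0.894 × 1.185 = 0.53 SD.
- r = 0.5 gives 0.31 and 0.57 SD; r = 0.8 gives 0.17 and 0.43 SD.

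The test arm looks about 0.26 SD worse than sham when the two are equal.

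**3. Second model, using the planning rates as selection rates.** Here the unit is the SD of the change, and the change at end of treatment correlates 0.3 to 0.7 with the change at follow-up.
- True follow-up change zero: the selected patients show +0.29 to +0.68 SD at a 40% selection rate, and +0.08 to +0.19 SD at 85%.
- Effect gone by follow-up: test minus sham is −0.21 to −0.49 SD instead of 0.
- Effect of 1.29 SD fully kept: test minus sham is 1.08 down to 0.80 SD instead of 1.29.

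Both models give a spurious gain within groups and a distorted contrast between groups.

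**The case against.** The strongest reply is that this is an add-on recording. The primary comparison is before versus after treatment, the questionnaires are not restricted by response, and asking whether responders keep their response is a legitimate descriptive question. That stands, and it limits the point to the 1- and 6-month HRV data. It does not rescue the stated purpose, which refers to the effects of the therapy and not to durability among responders. Durability measured from baseline is itself inflated by regression to the mean.

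Several stronger readings are tempting but not supported:

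- **That a between-arm test of follow-up HRV is planned.** The Statistical analysis section does not say so. The bias in section 2 of the working arises only if such a contrast is made.
- **That non-responders drop out of follow-up.** They are still followed by questionnaire; it is the ECG that they do not receive.
- **That the number selected is known.** Applying the planning rates to 30 per arm gives 25.5, 12 and 14.1, or 51.6 in all (46.4 on 27 per arm). But those rates belong to an effective rate that Statistical methods does not define, not to this two-part condition. They are a rough proxy, and no claim about the number of recordings can rest on them.

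Two further limits stand. The word only is not printed; it is the natural reading, since the condition would otherwise have no function. The schedule figure is not available here; if it lists HRV at follow-up for everyone, it conflicts with this section and the text still needs correcting. Also, the calculations select on HRV change alone, whereas the rule adds symptom improvement. The documents do not allow the joint effect to be calculated.

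**Conclusion.** The point holds for the follow-up HRV recordings: as written, they are selected on response, including response on the primary outcome, and cannot show the long-term effect that the section gives as their purpose. An apparent retained gain of 0.25 to 0.40 SD can arise with no treatment effect. That rests on selection of the half with the largest rise and on correlations of 0.8 to 0.5, and it is an illustration, not an estimate for this trial. Any between-arm contrast at follow-up would be biased by an amount that depends on unknown response rates and thresholds.

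A reader might infer that the trial's main result is compromised. It is not: HRV at end of treatment is measured without any response condition. Severity is therefore should-fix.

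**What to change.** Decide who has the follow-up ECG independently of response, and state it in the section Follow-up observation. Either of these would do:

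1. **All participants** at 1 and 6 months, compared by randomised arm. This means up to 90 recordings per visit, or 81 after the planned 10% loss.
2. **A random subset of equal size per arm**, fixed at randomisation and compared by randomised arm. Precision would be limited. With, for example, 17 per arm, a two-arm comparison at 80% power and two-sided 5% detects about (1.96 + 0.84) × √(2/17) = 0.96 SD, so roughly 1 SD, before dropout.

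Both options require some patients to attend in person who would otherwise be telephoned, and possibly more recordings than the current rule would produce. That number is unknown, so the change cannot be called cost-neutral.

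If neither is feasible, delete the long-term HRV effect as a purpose. Report the recordings as descriptive of responders only, with no group comparison and no claim of retained benefit. This costs a change of wording and the long-term HRV claim.
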